### 2.2. Participants and Recruitment

The targeted population is preschool-enrolled children recruited through kindergartens. Eligible participants will be 4 to 5 years old and need to meet all the following criteria: (1) being healthy and (2) have the permission of their parent or guardian to participate in this study; written informed consent will be obtained. We will exclude individuals who have (1) severe cognitive impairment, (2) major medical or physical conditions affecting their participation in physical exercise, or (3) motor development delay. There will be no restrictions regarding the sex, ethnicity, or socioeconomic status of any of the participants.

### 2.3. Randomization and Masking

First, the information of the recruited kindergarten will be obtained, including the name of classes, and the number of children in each class. Then, an opaque envelope will be used for simple random assignment, and recruited kindergartens as a unit will be randomly assigned to one of five groups. The generation of the random assignment will be completed by the main person who is in charge of the intervention. As this is a behavioral and skill-specific intervention, eligible children in the same class will receive an identical strategy to avoid confounding influences, such as different exercise instruments or teachers. Furthermore, details of the intervention group allocation will not be available to participants and their teachers. Data analysts will not include blind processing, which will be performed by two separate individuals for statistical analysis of the research results. Participants and teachers will be unblinded when the research is finished by providing a simple report and brochure to the kindergarten.

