## 2. Methods

### 2.1. Study Design

The study is a single-blind, cluster-RCT study, with the kindergarten class as the cluster for the intervention. This study is a part of the Physical Exercise on FMSs and PF of preschoolers (PEFP) project. The PEFP project is a series of studies, including a cross-sectional survey (covering six provincial and municipal regions in China) and the aforementioned RCT (implemented in Putuo District, Shanghai, China). Preschoolers recruited from 5 kindergartens will be cluster-randomly allocated to 5 groups (i.e., four intervention groups and one control group). The intervention groups are (1) the BG group, consisting of football, basketball games, etc.; (2) the RA group, including cheerleading, rhythm exercise, etc.; (3) the BM group, consisting of different basic movements, such as walking, running, jumping, climbing, throwing, catching, etc.; and (4) the MA group, combination of all kinds of physical exercise that have been used in other intervention studies. The control group (control) is an unorganized PA group (Figure 1). The content of the intervention comes from previous research combined with consultation and interviews with preschool educators [7,37].

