## 4. Statistical Analysis

### 4.1. Sample Size

The primary outcome variables in this study are FMSs and PF. Before recruitment, a priori power analysis was performed in G*Power 3.1 to calculate the sample size necessary to detect meaningful changes from the baseline to the post-intervention time points in the total raw scores of seven FMSs (i.e., 10-m shuttle-run, hopping, bouncing a ball, jamming coins, kicking, balance beam, and one-leg stand) and seven PF (i.e., balance beam, handgrip, standing long jump, sit-and-reach, 10-m shuttle running, 20-m shuttle running, handgrip strength, and hopping). Using an alpha of 0.05 and a power of 80%, the calculation of the power to detect a pre-post change in these measures was based on the effect sizes reported in a recent systematic review. The expected effect size of the intervention on FMSs and PF was at 1.42 and 0.36 (standardized mean difference, SMD), respectively [51]. With reference to these results, a prudent estimation of the effect size (SMD = 0.36) was used for the calculation. The required sample was calculated to be 70. To account for the clustering effect, this number was then multiplied by a design effect (DE) of 1 + (*m* − 1) × ICC, where *m* is the average cluster size and ICC was estimated at 0.05. With an estimated average class size of 30, at least 150 participants will have to be recruited. Based on previous studies, we presumed a drop-out rate of 15%, implying a minimal sample size of 150/0.85 = 176 children in total. This study takes the class as the cluster of random sampling; the class size in recruited kindergartens is 30–35. Therefore, considering the drop-out rate and special samples (preschool children with developmental retardation or hyperactivity disorder), each experimental group was divided into two classes, implying about 60 children in each group. The total size is 300.

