## 7. Challenges and Limitations

The current protocol has some challenges. First, the participants in this study are 4-–5-year-old preschool children who still largely lack self-control and attentional focus. It will, therefore, be difficult to engage them continuously in the designed physical exercise program. To meet this challenge, the research group will staff each intervention group with two researchers to ensure preschool children’s safety and the intervention quality. Second, the intervention will last for 16 weeks, which will place a great human resource pressure on the PEFP group. We plan to stagger the intervention time of two close kindergartens, and the intervention will be carried out between 8:30 and 11:30 in the morning. In this way, the researchers assigned by the PEFP group can assist more intervention groups within the time allowed.

There are some limitations to this protocol. First, young children are in a rapid period of growth and development; thus, it will be difficult to identify whether natural growth or the exercises intervention contributes to the improvement in children’s FMSs and PF. Like other studies, this protocol will set up a control group in the same school with each intervention group to reduce the confounding impact of natural growth as much as possible. Second, the intervention in this study will last 16 weeks, which seems insufficient to improve FMSs and PF. However, the duration of FMSs or PF interventions in previous studies varied from eight weeks to one academic year or longer [32,41,52,53].

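### The protocol contradicts itself on the unit of randomisation; under section 2.3 each arm is a single kindergarten, and arm effects on change cannot be separated from school effects on change

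*Protocol article*

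**What the plan says.** Four places in the protocol article bear on the unit.

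- Section 2.3, the only description of how allocation is carried out, says that "recruited kindergartens as a unit will be randomly assigned to one of five groups". The method is that "an opaque envelope will be used for simple random assignment".
- Section 2.1 says "Preschoolers recruited from 5 kindergartens will be cluster-randomly allocated to 5 groups", and describes the design as a cluster trial "with the kindergarten class as the cluster for the intervention".
- Section 4.1 says "This study takes the class as the cluster of random sampling", and that "each experimental group was divided into two classes, implying about 60 children in each group", for a total of 300.
- Section 7, on natural growth, says that "this protocol will set up a control group in the same school with each intervention group".

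The primary mixed model in section 4.4 has time, programme and their interaction as fixed effects, and kindergarten and individual as random effects. It has no class term. Age, sex and baseline FMS, PF and PA are prespecified covariates.

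**The concern.** The sections describe different trials. Read with the counts in 2.1, the rule in 2.3 leaves the randomised unit without replication: each arm is one school, and the two classes per arm in 4.1 are two classes of that school. Kindergarten teachers deliver the lessons (section 3.2.1), so the quality of teaching, the facilities and local events over the 16 weeks all differ by school. With one school per arm these cannot be told apart from the programme. Both aims in section 1, each programme against control and programme against programme, would then be comparisons of single schools.

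If the class is the unit, section 2.3 is wrong, and section 4.4 leaves the randomised unit out of its random effects. The document needs correcting on either reading.

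**Working it through.** **Headcount.** 5 arms x 2 classes x 30 children = 300, which reproduces the total in 4.1. It does not settle the unit, since the two classes of an arm may lie in one kindergarten or in two.

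**The schemes side by side.**

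- Kindergarten as unit (2.3 with the counts in 2.1): one kindergarten per arm, so no school contains both an intervention arm and the control arm. The sentence in section 7 is then impossible.
- Class as unit (2.1, 4.1): ten classes, two per arm. The control arm has two classes, which can sit in at most two of the five kindergartens. Intervention classes in the other three would have no control in their school, so section 7 does not fit here either.

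**Aliasing under 2.3.** Degrees of freedom for kindergarten within arm = 5 - 5 = 0. The arm indicators have rank 5, and adding the kindergarten indicators leaves the rank at 5. Arm and kindergarten are the same variable.

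**What the model in 4.4 can and cannot do.** A stable school difference in level is present at baseline and afterwards. It cancels from the time-by-arm contrast and is also addressed by the baseline covariates. A school difference in change does not cancel. A kindergarten random intercept describes level only, and with one kindergarten per arm its variance cannot be estimated separately from the arm effect. The arm contrast on change therefore carries no allowance for school.

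**Size if 2.3 is followed.** Inputs: 60 children per arm (4.1), two-sided 5% test. The ICC of 0.05 in 4.1 is tied to a class of 30, and the document gives none for kindergartens. The kindergarten ICC of the analysed (baseline-adjusted or change) outcome is therefore an assumption, shown over a range.

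- Design effect: DE = 1 + (60 - 1) x ICC
- Type I error if the school effect is ignored: 2 x [1 - Phi(1.96 / sqrt(DE))]
- Floor on the standard error of an arm contrast, however many children are tested: sqrt(2 x ICC), in SD units

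| Assumed kindergarten ICC | DE | Type I error per contrast | SE floor (SD) |
|---|---|---|---|
| 0.01 | 1.59 | 0.12 | 0.14 |
| 0.02 | 2.18 | 0.18 | 0.20 |
| 0.05 | 3.95 | 0.32 | 0.32 |
| 0.10 | 6.90 | 0.46 | 0.45 |

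The planning effect in 4.1 is an SMD of 0.36.

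**Would analysing class means help?** With two classes per arm in the same school, a class-level t test has 10 - 5 = 5 df. In 100,000 simulated trials with no programme effect and a total ICC of 0.05, it rejected in about 0.26 when the whole ICC lay between kindergartens and 0.12 when it was split equally between kindergartens and classes. It held 0.05 only when kindergartens did not differ.

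**The case against.** The strongest reply is that the class is the intended unit and 2.3 is loosely worded. Section 2.3 itself collects class names and sizes and treats all eligible children in a class alike. The count of five kindergartens comes from 2.1, not 2.3, and the design figure is not available here. This stands as far as it goes: a reader might infer that the trial certainly has one school per arm and cannot answer its aims, but the document does not establish that. It establishes that the only stated allocation rule leads there while other sections say otherwise.

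The second reply is that the analysis adjusts for baseline. This also stands in part. A reader might infer that any difference in starting level between two schools would appear as a programme effect. Section 4.4 does not support that, because its interaction term and covariates address stable level differences. What remains is confounding of change.

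Third, the error rates rest on an ICC that the document does not give for kindergartens, and a test that ignores school is not what 4.4 names. That is why a range is shown. No single value, such as 0.32, should be read as the trial's error rate. The named random effect is nevertheless no protection when each arm has one kindergarten.

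Section 2.3 also says "The generation of the random assignment will be completed by the main person who is in charge of the intervention". That is a separate weakness in concealment and does not bear on the aliasing.

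**Conclusion.** The contradiction is certain from the text and must be resolved before allocation. The confounding is conditional: if whole kindergartens are allocated as 2.3 says, there are 0 df for kindergarten within arm, and school-specific differences in 16-week change cannot be separated from the arm effect by any model. Ignoring them gives a type I error of about 0.12, 0.18, 0.32 and 0.46 per arm-versus-control contrast at assumed kindergarten ICCs of 0.01, 0.02, 0.05 and 0.10. These figures assume 60 analysed children per arm and an ICC that applies to the outcome as analysed. If classes are randomised across kindergartens, the aliasing disappears, but 2.3, 4.4 and 7 are then wrong as written.

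**What to change.** Before allocation, state one unit of randomisation consistently in 2.1, 2.3, 4.1, 4.4 and 7. The preferred form is:

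- Randomise the ten classes by restricted allocation, two per arm. Simple assignment does not guarantee two per arm.
- Place an arm's two classes in different kindergartens, and choose the layout so that all five arms are connected through shared kindergartens.
- Add class as a random effect in 4.4, with small-sample degrees of freedom. Leaving it out, with DE = 1 + 29 x 0.05 = 2.45, would give a type I error of 2 x [1 - Phi(1.96 / sqrt(2.45))], about 0.21.
- Have the sequence generated by someone who does not run the intervention. The data safety officer does not fit as section 4.3 stands, because that role is kept from the details of the research.
- Correct the same-school control sentence in section 7.

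This needs a protocol amendment and no further classes or children, but it has costs that should be stated. Contamination between classes in one school becomes possible, and masking there is weaker. Each arm is delivered at two sites, while section 7 already reports pressure on staff. Few degrees of freedom remain: 10 - 1 - 4 - 4 = 1 with kindergarten as a fixed block (critical t 12.7), or about 10 - 5 = 5 with class-level inference and no fixed block. Precision is therefore low. At the class ICC of 0.05, an unadjusted arm contrast has SE sqrt(2/60 x 2.45) = 0.29 SD, against a planning effect of 0.36. More classes or kindergartens would be stronger.

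If allocation by kindergarten is kept, state that arm and kindergarten are confounded, and withdraw the causal conclusions and the claim to identify the best programme.

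### The person in charge of the intervention generates the assignment, so concealment is not assured, and simple random assignment as worded does not guarantee two classes per arm

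*Protocol article*

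**What the plan says.** All references are to the protocol article.

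- **Who generates the assignment (2.3):** "The generation of the random assignment will be completed by the main person who is in charge of the intervention".
- **Method (2.3):** "an opaque envelope will be used for simple random assignment".
- **What is known beforehand (2.3):** "First, the information of the recruited kindergarten will be obtained, including the name of classes, and the number of children in each class". The sentence is passive and does not say who gathers this information.
- **Unit of allocation:** section 2.3 says "recruited kindergartens as a unit will be randomly assigned to one of five groups". Section 2.1 describes the trial as a cluster design "with the kindergarten class as the cluster for the intervention", yet adds "Preschoolers recruited from 5 kindergartens will be cluster-randomly allocated to 5 groups". Section 7 (Challenges and Limitations) places a control group in the same school as each intervention group.
- **Planned layout (4.1):** "each experimental group was divided into two classes, implying about 60 children in each group", and "The total size is 300".

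The article describes no blocking, restriction or draw without replacement. It names no independent generator or holder of the sequence, and it does not place release of the allocation after consent or baseline testing.

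**The concern.** Two stated choices are weak.

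**Independence.** The person responsible for the intervention also produces the assignment, at a point when the classes and their sizes are already listed. An opaque envelope stops other people from foreseeing an assignment. It gives no protection against the person who prepared it. The Background predicts a direction: every programme should beat unorganized activity, and multiple activities should beat the other three. Whoever leads the intervention therefore has an interest in where the multiple-activities and control labels fall. With five kindergartens or ten classes in the whole trial, the placement of a single unit is a large part of an arm, and no later analysis can repair a compromised assignment.

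**Method against layout.** Simple random assignment, in its usual technical sense, draws each unit's arm independently. With so few units that rarely produces equal arms and can leave an arm empty, whereas section 4.1 plans two classes in every group.

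**Working it through.** **Inputs.** Five arms and five kindergartens (2.1); two classes per group, about 60 children per group, total 300 (4.1); average class size 30 (4.1); simple random assignment (2.3). Equal assignment probabilities of 1/5 are assumed, since the article gives no ratio other than equal group sizes.

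**The plan's own figure.** 5 arms × 2 classes × 30 children = 300. This reproduces the stated total and implies ten classes.

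**Literal simple assignment, class as unit (ten classes).**

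- Exactly two per arm: 10!/((2!)^5 × 5^10) = 113,400/9,765,625 = 0.0116, or 1.2%.
- At least one empty arm, by inclusion–exclusion: 5(0.8)^10 − 10(0.6)^10 + 10(0.4)^10 − 5(0.2)^10 = 0.477, or 47.7%.

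**Literal simple assignment, kindergarten as unit (five kindergartens).**

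- One per arm: 5!/5^5 = 120/3,125 = 0.0384, or 3.8%.
- No kindergarten in control: 0.8^5 = 0.328, or 32.8%.

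**Restricted draw for comparison.** Suppose each arm's label is placed in exactly two of ten class envelopes, or in one of five kindergarten envelopes, and drawn without replacement. Equal arms are then certain. There remain 10!/(2!)^5 = 113,400 possible allocations of classes, or 5! = 120 of kindergartens. Restriction therefore costs nothing in randomness that matters here.

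**The unit.** The restricted list cannot be written until the unit is fixed:

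| Place | Unit implied |
|---|---|
| 2.1 | Class is the cluster, but five kindergartens go to five groups |
| 2.3 | Kindergarten |
| 4.1 | Class, two per group |
| 7 | Control in the same school as each intervention group |

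If whole kindergartens are assigned one per arm, two classes per arm follow only if each kindergarten supplies two classes, which is an assumption. A control group inside each intervention school cannot coexist with kindergartens assigned as a unit.

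**Independence.** No arithmetic applies. Section 2.3 gives generation to the intervention lead in plain words, and nothing elsewhere in the article moves generation, holding or release to anyone else.

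**The case against.** The strongest reply has five parts.

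1. **An opaque envelope is a concealment device.** A reader might infer from the lead's role that allocation is unconcealed. The article does not support that: generation and concealment are separate steps, and details such as sealing, numbering and custody are commonly left to the full protocol. This stands. What remains is that the one role the article does assign goes to the wrong person, so concealment is not assured.
2. **Simple may be used loosely.** Five kindergartens, five groups, an envelope and a fixed layout are compatible with drawing lots without replacement, which gives equal arms. A reader might infer that the method cannot deliver two classes per arm, but that goes too far. The method as worded does not guarantee it. The percentages above apply to the literal reading only.
3. **Listing classes before allocation is normal in a cluster trial.** That is correct. A reader might also infer that the intervention lead collects the list; section 2.3 does not say so. The difficulty is only that generation follows the listing and sits with the lead.
4. **Testers are kept unaware of allocation (4.2).** This helps protect outcome measurement. It does not protect the assignment itself.
5. **Chance differences between clusters are not a measure of this defect.** It is tempting to set sqrt(2 × 0.05) = 0.32, from the planned ICC applied to two kindergartens, beside the planning effect of 0.36. That variation exists under perfect randomization too, and the fix would not reduce it. It also moves the ICC from the class level used in 4.1; with two classes per arm the figure would be sqrt(2 × 0.05/2) = 0.22. Neither figure is used here.

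**Conclusion.** The point holds in two limited statements.

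First, generation is expressly given to the person in charge of the intervention, after the classes and their sizes are known, and no independent generator or holder is named. Allocation is not independent of the intervention team. This rests on the text of 2.3 alone. The resulting bias cannot be quantified from the article.

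Second, simple random assignment as written does not guarantee the layout of 4.1. Under the literal reading, with equal and independent probabilities, the planned balance occurs with probability 1.2% for ten classes or 3.8% for five kindergartens. If lots are drawn without replacement, the defect is one of wording only.

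Both should be corrected before allocation takes place.

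**What to change.** 1. **Reconcile the unit of allocation** across 2.1, 2.3, 4.1 and 7, and state it once.
2. **Move generation and custody** to someone outside the intervention team, for example a project statistician not involved in delivery. Remove the intervention lead from generation in 2.3. The data safety officer is not an obvious choice, because 4.3 says that officer will not obtain the details of the research.
3. **Replace simple assignment** with a restricted equal-allocation list of the reconciled unit. For example, each arm's label would appear the same number of times and be drawn without replacement.
4. **State the timing:** the list is released only after consent and baseline testing. Section 3.2.1 has pilot lessons given according to the randomized group before the formal study, so that sentence must be made consistent with the release date.

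The cost is small: a change of wording and a little time from someone already in the project. The one practical drawback is that allocation becomes known slightly later for planning teacher training.

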### 4.2. Data Collection

The test will be conducted by members of the PEFP research group, who have no competing interests, and details of the intervention group allocation will not be available to the testers. Before the test, two training sessions will be conducted to ensure the quality of the test, which will be conducted by professionals from the test equipment company. The workshop will (1) cover the development characteristics and special needs of young children; and (2) deliver the basic concepts, testing skills, and emergency plans for young children.

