### 4.3. Data Management

All research data entry will be carried out by two people, followed by an interrater consistency check. Consent forms will be stored separately from participant data, and a unique identifier code will be assigned to each participant. Data will be deleted immediately from voice recorders after the transcription, with pseudonyms used in all reports in place of participants’ names. Data will only be accessible to primary researchers and statisticians after application to the research group. Data will be stored for a maximum of 5 years before being securely destroyed.

All phases of this study will be monitored by a data safety officer, who has worked for monitoring data collection and data analysis. The data safety officer is responsible for the data management and distribution of applied data, and will not obtain the details of the research. Management of the trial data will be in accordance with the data management plan, which was developed and approved by the project group. Moreover, the data will be published in two ways: writing academic papers and uploading to the experiment registration website.

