### 4.4. Data Analysis Plan

Baseline characteristics and unadjusted study outcome measures will be summarized by intervention groups using descriptive statistics and used to assess between-group equivalence at baseline. Prespecified baseline covariates in both primary and secondary outcome analyses will include age, sex, FMSs capacity, PF level, and PA level.

Baseline demographic descriptors and primary and secondary outcome measures will be compared across groups by using analysis of variance (a non-parametric test will be used when the data does not conform with a normal distribution) for continuous variables and the χ^2^ test for categorical variables. The planned descriptive data on measured-point FMSs and PF will be tabulated across the intervention groups and control group. In our primary analysis of the FMSs and PF outcome, we will use mixed model analyses to estimate the differences with their corresponding 95% CIs, comparing the BA, RA, BM, and MA groups with the control group. Time, physical exercise programs (intervention or control groups), and their interaction will be fixed factors. The random effects will be the kindergarten and individual to take into account the clustered data structure.

Multilevel linear regression models will be constructed to assess the effectiveness of the physical exercises on FMSs and PF performance. The baseline data of the outcome variables, assessment points, intervention groups, and any imbalanced covariance will be added to the model along with the kindergartens and PA as random effects. The interaction between physical exercise and FMSs and PF will be tested.

Secondary analyses will investigate the effect of the intervention on other domains using different types of regression analyses, depending on the outcomes. Logistic regressive analyses will be constructed to assess the interference factors. The models will be used to assess the effect of forms of physical exercise, and to explore associations between secondary outcome measures, and will be adjusted for various confounding factors (e.g., sex, PA).

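### Section 2.3 most naturally leaves the two analysts unmasked, while Section 4.4 leaves the covariates and the choice of primary model for FMSs and PF open

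*Protocol article*

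**What the plan says.** **Masking.** Section 2.1 begins: "The study is a single-blind, cluster-RCT study, with the kindergarten class as the cluster for the intervention". It does not say which party the single-blind label refers to. Section 4.2 masks the outcome testers: "details of the intervention group allocation will not be available to the testers". Section 2.3 says the same of children and teachers: "details of the intervention group allocation will not be available to participants and their teachers". On the analysis, the operative words in Section 2.3 are "Data analysts will not include blind processing"; the sentence in full reads: "Data analysts will not include blind processing, which will be performed by two separate individuals for statistical analysis of the research results". It gives no reason.

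**Analysis.** Section 4.4 lists prespecified baseline covariates for the primary and secondary analyses: age, sex, FMSs, PF and physical activity (PA). For FMSs and PF it then gives two models:
- a mixed model with time, programme and their interaction as fixed factors, and kindergarten and individual as random effects; this one is introduced as the primary analysis;
- a multilevel linear regression to assess effectiveness on the same outcomes, adjusted for the baseline outcome, where "any imbalanced covariance will be added to the model along with the kindergartens and PA as random effects".

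**Data flow.** Section 4.3 says: "The data safety officer is responsible for the data management and distribution of applied data". It adds that this officer does not obtain the details of the research.

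**The concern.** The Background commits the trial to a direction: organised programmes should beat unorganised activity, and the multiple-activities arm should beat the other three. An analyst who sees arm labels while deciding which covariates count as imbalanced, or which of two models to put forward, can see which option supports that ordering. No bad faith is needed for this to tilt the result. At stake is the credibility of the four comparisons with control on the two primary outcomes. The protocol already routes data through an officer, so much of this exposure can be avoided.

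**Working it through.** The plan gives no figure on this point, so there is none to reproduce. The check compares passages and adds one illustration.

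**1. Are the analysts masked?** Masking is stated for testers (4.2) and for children and teachers (2.3). Coded arms or masked analysts are mentioned nowhere. The Section 2.3 sentence allows two readings: the two people doing the analysis are not masked, or the masking step is done by two people other than the analysts. The first is more natural, and nothing elsewhere supports the second.

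**2. Which open choices in Section 4.4 reach FMSs and PF?**

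| Text in 4.4 | Applies to | Reaches the primary outcome models? |
|---|---|---|
| Adding imbalanced covariates | Multilevel model for FMSs and PF | Yes |
| Two models, precedence not settled | FMSs and PF | Yes |
| Non-parametric test if not normal | Comparison of baseline descriptors and outcome measures across groups | No |
| Regression type depending on outcome | Secondary analyses of other domains | No |
| Open list of confounders | Secondary models | No |

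Two choices matter. The first conflicts with the prespecified list: the list fixes the covariates, and the imbalance rule reopens them without defining imbalance. On the second, the mixed model carries the word primary, but the multilevel model is assigned the effectiveness question itself, with different adjustment and random effects. The text does not say which result decides.

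**3. Would coding the arms be enough?** This is an illustration under assumptions. Take one contrast with no true effect and two candidate analyses with test statistics a ~ N(0,1) and b = ρa + √(1 − ρ²)·e, where e ~ N(0,1) is independent of a. The threshold is 1.96 (alpha 0.05 from Section 4.1; two-sided is assumed). With labels visible, the analyst keeps max(a, b), the result more favourable to the active arm. With arms coded, the analyst keeps whichever is larger in absolute value, that is, the smaller p-value. There were 1,000,000 draws per ρ, and the values of ρ are assumed.

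| ρ | One prespecified analysis, favouring active | Labels visible, favouring active | Arms coded, favouring active | Arms coded, either direction |
|---|---|---|---|---|
| 0.5 | 2.5% | 4.5% | 4.5% | 9.0% |
| 0.7 | 2.5% | 4.2% | 4.2% | 8.4% |
| 0.9 | 2.5% | 3.5% | 3.5% | 7.0% |

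Coding prevents steering towards a named arm. It does not prevent selection by p-value, and the false-positive rate in favour of the active arm is then the same as with labels. Fixing the analysis in advance brings it back to 2.5%.

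**4. Would coding arms alone mask?** Sections 2.1 and 2.3 allocate five kindergartens, as units, to five groups, and 4.4 uses kindergarten as a random effect. On that wording there is about one kindergarten per arm, so an uncoded kindergarten identifier reveals the arm. The primary contrasts are also against control, so an analyst under code must either have the control code opened or run all pairs: 5 × 4 / 2 = 10 contrasts, six more than the four against control.

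**The case against.** The strongest reply is that this is mainly a prespecification problem. The Section 2.3 sentence is ambiguous, the trial is declared single-blind, the testers are masked, and most outcomes are timed or measured. A covariate list is already prespecified, and a statistical analysis plan that is not shown may settle the rest.

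Much of this stands. Four stronger inferences are not supported:
- A reader might take it as settled that the analysts are unmasked. That is only the more natural reading.
- A reader might count the normality switch and the outcome-dependent regression type as further discretion over the primary outcomes. The first belongs to the across-group comparison and the second to secondary analyses, and both are commonly left to an analysis plan.
- A reader might conclude that coded arms would remove the problem at no cost. Steps 3 and 4 of the working show otherwise.
- A reader might infer that the data safety officer holds the participants' identifier codes. Section 4.3 says that codes are assigned but names no holder.

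What the reply does not answer is that the imbalance rule is written in the protocol itself, against its own list, and that neither reading of the Section 2.3 sentence tells the reader what the analysts will know. Masked testers protect the measurement of outcomes, not the choice of model.

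**Conclusion.** The point holds as a low-severity, inexpensive improvement. On its most natural reading the protocol leaves the analysts unmasked, while two choices affecting FMSs and PF remain open under a directional hypothesis. The document shows an opportunity for bias, not bias itself, and its size cannot be computed from the document. The 3.5% to 4.5% range against 2.5% rests on one contrast, two candidate analyses, assumed correlations of 0.5 to 0.9, and an analyst who always keeps the more favourable result. It shows how the mechanism works and is not an estimate for this trial. Masking and prespecification are both needed.

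**What to change.** **Section 2.3.** Replace the sentence with a plain statement along these lines: the two analysts receive data in which both arm and kindergarten identifiers are coded; the file is released through the data safety officer; any data that would reveal the arm are held back; and the code stays closed until the primary models have been run. Either all ten pairwise contrasts are run under code, or the control code is opened only after the models are locked. Name who holds the key, since Section 4.3 says the officer does not obtain the details of the research.

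**Section 4.4.** Remove the provision that "any imbalanced covariance will be added to the model" and use the prespecified list (age, sex, baseline FMSs, PF and PA). Name one of the two models as primary for FMSs and PF and label the other as supportive. Both decisions must be fixed before any between-group outcome result is seen.

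**Cost.** A few sentences of text, one recoding step by existing staff, and up to six extra contrasts if all pairs are run. These six are the comparisons among the four programmes, which the trial's second aim already calls for. No change to recruitment, intervention or measurement is needed.
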